## Abstract

**Background:**

Depression is common among elective lumbar spine surgery candidates and is associated with worse postoperative outcomes. Home-based transcranial direct current stimulation (tDCS) has demonstrated safety and feasibility, with evidence of antidepressant effects in remote randomized and open-label studies of major depressive disorder (MDD). Whether this approach can be feasibly and acceptably implemented as a preoperative intervention in lumbar spine surgical populations is unknown.

**Methods:**

We propose a prospective, open-label, single-arm feasibility study evaluating preoperative, home-based tDCS for elective, non-revision lumbar spine surgery candidates with MDD. Adults aged 22–75 years with DSM-5 MDD and at least moderate depressive symptom severity [self-reported Montgomery–Åsberg Depression Rating Scale (MADRS-S) ≥ 20] being evaluated for elective lumbar spine surgery will receive home-based tDCS. Key exclusion criteria include history of seizure disorder, implanted cranial electronic or metallic devices, clinically unstable psychiatric conditions, prior brain stimulation therapy, and use of medications that significantly affect cortical excitability. Pre-surgical treatment follows a standardized cadence (5 sessions/week for 3 weeks, then 3 sessions/week) for a minimum of 4 weeks, continuing until surgery or up to 10 weeks. Feasibility will be assessed using a pre-specified tiered exposure framework based on the number of sessions completed before surgery.

**Anticipated results:**

Primary outcomes are feasibility and acceptability of preoperative home-based tDCS delivery. The principal exploratory clinical outcome is change in depressive symptom severity measured using MADRS-S. Exploratory perioperative recovery outcomes include spine-related disability, pain intensity, functional status, and opioid utilization. For participants who proceed to surgery, postoperative outcomes will be followed up to 12 months.

**Discussion:**

This pilot study will generate feasibility, acceptability, and preliminary signal data to inform the design of future randomized controlled trials of preoperative neuromodulation in surgical populations.

## Introduction

Depressive symptoms are common among patients presenting for elective lumbar spine surgery and represent an under-addressed determinant of perioperative recovery (Kim et al., 2017; Javeed et al., 2024; Xu et al., 2026; O’Callaghan et al., 2026). Across spine populations, a substantial proportion of surgical candidates report clinically meaningful depressive symptoms at the time of evaluation, frequently in the setting of chronic pain and functional limitation. Importantly, this burden is evident even among patients without a formal psychiatric diagnosis, underscoring the clinical relevance of subsyndromal depressive symptoms in surgical care.

Depression in spine surgery candidates has been consistently associated with higher pain intensity, greater disability, and worse health-related quality of life at baseline (Kim et al., 2017; Javeed et al., 2024; Xu et al., 2026; O’Callaghan et al., 2026). Postoperatively, depressive symptoms have been linked to lower patient satisfaction, delayed functional recovery, and less favorable patient-reported outcomes. Depression has also been associated with increased perioperative opioid utilization and a greater likelihood of persistent opioid use after surgery, suggesting that mood disturbance may influence pain coping behaviors and recovery trajectories. Collectively, these findings position depression not merely as a comorbidity but as a potentially modifiable factor that shapes surgical outcomes.

The perioperative period represents a distinct opportunity for intervention. In elective lumbar surgery, the interval between surgical decision-making and operative intervention provides a predictable window during which targeted prehabilitation strategies can be implemented. While physical prehabilitation has received increasing attention, systematic approaches to optimizing mental health before spine surgery remain limited. Interventions that are scalable, remotely deliverable, and easily integrated into existing care pathways are particularly well suited to this setting.

Transcranial direct current stimulation (tDCS) is a noninvasive neuromodulation technique with established relevance to major depressive disorder. Bifrontal tDCS targeting the dorsolateral prefrontal cortex modulates cortical excitability and frontolimbic networks implicated in mood regulation, cognitive control, and pain processing. As a non-pharmacologic intervention, tDCS avoids medication-related adverse effects and drug–drug interactions that may complicate perioperative care. Its safety profile is favorable, with adverse effects typically mild and transient (Woodham et al., 2025).

Recent advances in device design, digital guidance, and remote supervision have enabled reliable home-based delivery of tDCS (Ruffini et al., 2024; Cappon et al., 2022). Clinical trials of home-based platforms have demonstrated feasibility, high adherence, and reductions in depressive symptom severity in both randomized and open-label settings, including fully remote implementations (Woodham et al., 2025; Borrione et al., 2024; Oh et al., 2023; Woodham et al., 2022; Moshfeghinia et al., 2025). These data support tDCS as a scalable intervention that can be deployed outside traditional psychiatric clinics, making it an attractive candidate for preoperative use (Aktürk et al., 2025).

The convergence of these clinical and technological developments makes elective lumbar spine surgery candidates with MDD a particularly well-suited population for home-based preoperative tDCS. First, the prevalence of clinically meaningful depressive symptoms is high in this cohort, and depression has a documented impact on perioperative outcomes including pain, function, and opioid utilization. Second, the elective surgical workflow provides a predictable, time-bounded preoperative window during which a structured intervention can be initiated and sustained. Third, home-based delivery is particularly relevant to spine surgery candidates, who often experience pain and functional limitations that may make repeated in-clinic visits burdensome. Fourth, the non-pharmacologic nature of tDCS avoids medication-related concerns that complicate perioperative pharmacotherapy decisions. Finally, the structured surgical care pathway provides a natural infrastructure for downstream outcome capture, enabling pragmatic evaluation of whether preoperative mood modulation is associated with recovery-relevant endpoints. Conceptually, reducing depressive symptom burden before surgery may improve pain coping, decrease pain interference, reduce opioid requirements, and support more favorable functional recovery. Despite this strong conceptual fit, the feasibility and acceptability of implementing home-based tDCS within the preoperative spine surgery pathway, and the extent to which sufficient treatment exposure can be achieved before surgery, remain unknown.

Before pursuing a definitive randomized controlled trial, foundational pilot data are needed. Specifically, it is necessary to determine whether preoperative home-based tDCS can be operationalized within the logistical constraints of elective spine surgery, whether patients can initiate and sustain treatment prior to surgery, and to obtain preliminary estimates of symptom change and variability. The present study addresses these gaps by evaluating the feasibility, acceptability, and preliminary clinical signal of preoperative home-based tDCS in elective, non-revision lumbar spine surgery candidates, informing the design of future controlled trials.

### Objectives and hypotheses

The primary objective of this study is to evaluate the feasibility and acceptability of delivering a home-based transcranial direct current stimulation (tDCS) intervention using the Flow Neuroscience device (Figures 1, 2) to patients with major depressive disorder (MDD) being evaluated for elective, non-revision lumbar spine surgery. The study aims to determine whether patients can successfully initiate and sustain a structured tDCS regimen during the preoperative period, despite variability in surgical timing and competing perioperative demands.

**Figure 1 fig1:**
[figure not shown]
Flow neuroscience headset (FL-100) (Flow neuroscience patient sign-up, 2026). Source: Images were reproduced, with permission, from the parent company - Flow Neuroscience.

**Figure 2 fig2:**
[figure not shown]
User wearing the flow neuroscience headset (Flow neuroscience patient sign-up, 2026). Source: Images were reproduced, with permission, from the parent company - Flow Neuroscience.

We hypothesize that most enrolled participants will be able to initiate treatment, defined as completion of the tDCS initiation phase within the first 3 weeks, and that a substantial proportion will achieve at least the minimum pre-specified treatment exposure before surgery. We further hypothesize that the intervention will be acceptable and well-tolerated, as reflected by high adherence, low rates of discontinuation due to adverse effects, and favorable participant-reported satisfaction.

A key exploratory clinical objective of the study is to assess preliminary changes in depressive symptom severity associated with preoperative home-based tDCS. The principal exploratory clinical outcome is change in depressive symptoms, measured using the self-reported Montgomery–Åsberg Depression Rating Scale (MADRS-S), consistent with prior home-based tDCS studies. We hypothesize that participants will demonstrate a reduction in depressive symptom severity from baseline to the preoperative assessment, with measurable improvement evident following completion of the intensive initiation phase.

Additional exploratory objectives include examining whether preoperative tDCS exposure is associated with changes in perioperative recovery-relevant outcomes. These exploratory outcomes include spine-related disability measured using the Oswestry Disability Index (ODI); back and leg pain intensity assessed via numeric rating scales; pain-related function measured using the PROMIS Pain Interference short form; and overall physical function measured using the PROMIS Physical Function short form. Opioid exposure will be assessed using standardized morphine milligram equivalent (MME) calculations, including baseline outpatient opioid use and postoperative opioid utilization across inpatient and outpatient settings.

In exploratory analyses, we hypothesize that greater tDCS exposure will be associated with larger reductions in depressive symptom severity and that participants demonstrating greater improvement in depressive symptoms may also exhibit lower opioid requirements and modest improvements in spine-related patient-reported outcomes. These analyses are intended to be hypothesis-generating and to inform outcome selection and effect size estimation for future controlled trials evaluating preoperative neuromodulation interventions in spine surgery populations.

This study is not powered to establish efficacy for clinical or surgical outcomes. Rather, it is designed to generate feasibility, acceptability, and preliminary signal data to guide the design of subsequent randomized studies.

## Methods and analysis

### Study design

This is a prospective, open-label, single-arm feasibility study evaluating home-based transcranial direct current stimulation (tDCS) using the Flow Neuroscience device as a preoperative intervention for patients with major depressive disorder (MDD) being evaluated for elective, non-revision lumbar spine surgery (Figure 3).

**Figure 3 fig3:**
[figure not shown]
CONSORT-style participant flow diagram. Participants are identified through spine surgery clinic schedules and screened for eligibility. Enrolled participants initiate home-based tDCS and are classified by pre-specified exposure tier based on the number of sessions completed. Following the intervention period, participants who proceed to elective lumbar spine surgery enter postoperative follow-up. Participants who do not proceed to surgery are followed for pre-operative and intervention-related outcomes only; postoperative recovery endpoints are not collected for this subgroup. All participants are included in the primary as-treated analysis by exposure tier achieved. Source: Images were reproduced, with permission, from the parent company - Flow Neuroscience.

The study is designed to prioritize feasibility and acceptability, with an exploratory assessment of changes in depressive symptom severity. Because the interval between surgical decision-making and operative intervention varies across patients, the intervention is delivered using a dose-to-time model with pre-specified exposure tiers based on the number of tDCS sessions completed before surgery.

As a pilot study, the design aims to (1) operationalize home-based neuromodulation within a perioperative spine surgery workflow, (2) quantify feasibility, acceptability, and safety, and (3) generate preliminary estimates of symptom change and variability to inform the design of future controlled trials. The protocol is reported in accordance with SPIRIT recommendations for interventional trial protocols (Supplementary Table S1).

### Setting

The study will be conducted at the Department of Neurosurgery and Department of Orthopaedic Surgery at Johns Hopkins Hospital, Baltimore, Maryland, United States. Enrollment is planned to begin in 2026, with completion of follow-up anticipated by 2027. Study procedures will be integrated with standard preoperative evaluation, perioperative care, and routine postoperative follow-up. The tDCS intervention is delivered in the home setting and supported through remote monitoring and scheduled study team check-ins. Study assessments may be completed in person or remotely, depending on clinical workflow and the timing of required measures.

### Eligibility criteria

Inclusion criteria:

1 Adults aged 22–75 years old2 Clinical diagnosis of unipolar major depressive disorder as determined by the patient’s established managing clinician3 At least moderate depressive symptom severity, defined as a baseline self-reported Montgomery–Åsberg Depression Rating Scale (MADRS-S) score ≥204 Being evaluated or scheduled for elective, non-revision lumbar spine surgery (prior spine surgery is not a contraindication)5 Either:

not receiving antidepressant medication, orreceiving antidepressant medication and/or psychotherapy at a stable dose or frequency for ≥6 weeks before enrollment, with agreement to maintain treatment stability during the study

6 Ability to use the Flow device independently at home and to complete remote assessments, including use of a smartphone or tablet to guide sessions and transmit adherence data7 Under the care of a primary care physician or mental health provider8 Capacity to provide informed consent

Exclusion criteria: Exclusion criteria are designed to ensure participant safety, minimize risks associated with electrical stimulation, and improve interpretability of study outcomes. Key exclusions include:

Neurologic and device-related exclusions

History of seizure disorder, epilepsy, loss of consciousness related to seizures, or other neurologic conditions that may increase riskPresence of implanted electronic or metallic devices (cranial or otherwise) that may pose safety concerns (e.g., pacemakers or implanted neurostimulators)Neurocranial defects

Psychiatric exclusions

Clinically unstable psychiatric conditions requiring urgent treatment (e.g., acute suicidality, psychosis, or mania)Current or past bipolar disorder, psychotic disorder, or obsessive-compulsive disorder

tDCS-specific and medication exclusions

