#### Exploratory clinical outcomes: depressive symptoms

Clinical outcomes are exploratory (Table 1). The principal exploratory clinical outcome is change in depressive symptom severity measured using MADRS-S. Depressive symptoms will be assessed at baseline (week 0) before initiation of tDCS, at week 1, at the end of the initiation phase (week 4), at week 7, and at a preoperative assessment conducted within a defined window before surgery (week 8–10+). Observed changes in depressive symptom severity will be interpreted in the context of the study’s feasibility-focused design. These analyses are not intended to establish efficacy, but rather to generate preliminary signal and variability estimates to inform future trial design.

**Table 1 tab1:** Exploratory outcomes.

Domain	Measure	Baseline	Timepoints*	Pre-op**	Post-op
Depression	MADRS-S	X	X	X	—
Spine disability	Oswestry disability index (ODI)	X	—	X	X (6 wks or 3 mos)
Pain intensity	Back pain NRS (0–10)	X	X	X	X
	Leg pain NRS (0–10)	X	X	X	X
Pain-related function	PROMIS pain interference (SF)	X	Optional	X	X
Physical function	PROMIS physical function (SF)	X	—	X	X
Opioid exposure	Baseline outpatient opioid use (MME)	X	—	—	—
Opioid utilization	Inpatient postoperative MME	—	—	—	X
	30-day outpatient postoperative MME	—	—	—	X

*Week(s) 0, 1, 4, 7, 10, and preoperatively (as applicable). **≤7 days before surgery.

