#### Exploratory clinical analyses: depressive symptoms

Exploratory analyses will evaluate changes in depressive symptom severity over time. The principal exploratory clinical outcome is the change in MADRS-S score from baseline to the preoperative assessment. Change from baseline to the end of the initiation phase (week 4) will be examined as an early signal of response following intensive treatment initiation.

Longitudinal changes in depressive symptoms will be examined using mixed-effects models to account for repeated measures and variable treatment exposure. Models will include fixed effects for time and baseline symptom severity, with random effects to account for within-participant correlation. These analyses are exploratory and not powered to establish efficacy. Exploratory response and remission rates based on standard MADRS-S thresholds will be summarized descriptively at the preoperative time point.

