## Discussion

This prospective pilot study is designed to evaluate the feasibility and acceptability of delivering home-based transcranial direct current stimulation (tDCS) as a preoperative intervention elective lumbar spine surgery candidates with MDD. The primary contribution of this work is implementation-focused: to determine whether a remotely delivered neuromodulation intervention can be initiated and sustained within the variable and time-constrained preoperative surgical workflow. By using a dose-to-time framework with pre-specified exposure tiers, this study addresses a practical challenge unique to elective surgery—heterogeneity in time from enrollment to operation—and provides a pragmatic model for preoperative mental health optimization.

Beyond feasibility, this study aims to generate preliminary estimates of depressive symptom change and variability using a validated self-report instrument (MADRS-S). These exploratory clinical data are not designed to establish efficacy, but rather to inform endpoint selection, assessment timing, and sample size assumptions for future trials. In addition, exploratory evaluation of perioperative recovery–relevant outcomes, including pain, disability, and opioid utilization, provides an initial signal as to whether preoperative mood modulation may be meaningfully related to downstream recovery trajectories.

Several anticipated challenges are inherent to this study design. Adherence may vary over longer preoperative intervals, and treatment exposure will be constrained by surgical scheduling. Concomitant changes in depression treatment during the preoperative period may introduce additional variability. Surgical heterogeneity and baseline differences in pain and disability further complicate the interpretation of exploratory recovery outcomes. These challenges are intentionally addressed through feasibility-first endpoints, as-treated analyses, tiered exposure definitions, and descriptive modeling approaches, which prioritize transparency and interpretability over causal inference.

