This study has important limitations. As an open-label, single-arm pilot, it is inherently susceptible to placebo and context effects, regression to the mean, and spontaneous symptom fluctuation. Selection bias is possible, as participants are limited to elective, non-revision lumbar spine surgery candidates who are able and willing to engage with a home-based digital intervention. Accordingly, findings may not generalize to emergent surgery, revision procedures, or other spine populations. These limitations are appropriate for an early-phase feasibility study and underscore the need for subsequent controlled evaluation.

The results of this study are intended to directly inform next steps. A logical extension is a randomized, sham-controlled or comparative effectiveness trial evaluating preoperative tDCS in surgical populations. Future work should also assess implementation outcomes, including scalability, cost-effectiveness, and integration into perioperative care pathways. Incorporating mechanistic or intermediate outcomes may further clarify links among mood modulation, pain processing, and recovery. Together, this pilot study represents a foundational step toward evaluating preoperative neuromodulation as a scalable strategy to optimize mental health and recovery in spine surgery.

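### The MADRS-S score used for entry (≥20) also serves as week-0 baseline, adding a reducible regression-to-the-mean component to the principal exploratory change outcome

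*Protocol article*

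**What the plan says.** Under Eligibility criteria, at least moderate severity is "defined as a baseline self-reported Montgomery–Åsberg Depression Rating Scale (MADRS-S) score" of 20 or more. Under Exploratory clinical outcomes: depressive symptoms, the only pre-treatment measurement is week 0: "Depressive symptoms will be assessed at baseline (week 0) before initiation of tDCS". Table 1 has one baseline column. The article describes no screening score distinct from week 0, no run-in and no repeat baseline.

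The analysis section then states: "The principal exploratory clinical outcome is the change in MADRS-S score from baseline to the preoperative assessment". The longitudinal model is specified as follows: "Models will include fixed effects for time and baseline symptom severity, with random effects to account for within-participant correlation". There is no comparator: "This is a prospective, open-label, single-arm feasibility study".

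The change estimate has a declared use. Under Objectives and hypotheses, the exploratory analyses are meant "to inform outcome selection and effect size estimation for future controlled trials evaluating preoperative neuromodulation interventions in spine surgery populations". The Discussion says that the depressive-symptom data serve "to inform endpoint selection, assessment timing, and sample size assumptions for future trials". On the limits of the design, the Discussion says of the open-label, single-arm pilot that "it is inherently susceptible to placebo and context effects, regression to the mean", among other things. It does not link this to the entry cut-off and gives no step to reduce it.

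**The concern.** As the article reads, one measurement does two jobs: it admits the participant and it starts the change. A lower cut-off on an imperfectly reliable score admits some people whose score was temporarily high. Their later scores drift back towards their usual level, so the mean change is negative even if the device does nothing. Baseline severity as a covariate does not correct this, because with no control arm there is nothing to set the mean change against.

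Regression to the mean comes partly from the natural course of illness and partly from selecting on the very score that serves as baseline. The second part is a choice about measurement, not a consequence of having one arm. At stake is a modest optimistic bias in the mean change that the study intends to pass on to later trials.

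**Working it through.** **The plan's own figure.** The article gives no precision or variability figure for MADRS-S change. Its only precision figure is a 95% interval width of about 0.34–0.40 for a proportion of 60%–80% with n = 20. The Wilson interval gives 0.395 at 12/20 and 0.335 at 16/20, so that figure reproduces. It does not bear on this point.

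**Inputs.** From the article: cut-off 20, the same score as qualifier and baseline, single arm, 20 evaluable participants. Assumed, because the article gives none: scores in the screened population are normal with mean μ and SD 8, and the correlation between occasions (reliability) is r.

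**Spurious fall when one score does both jobs.** With a = (20 − μ)/SD and λ = φ(a)/(1 − Φ(a)), the mean qualifying score exceeds μ by SD × λ, and the expected fall with no treatment effect is (1 − r) × SD × λ.

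| Assumed μ | λ | SD × λ | r = 0.9 | r = 0.8 | r = 0.7 |
|---|---|---|---|---|---|
| 14 | 1.329 | 10.63 | 1.06 | 2.13 | 3.19 |
| 20 | 0.798 | 6.38 | 0.64 | 1.28 | 1.91 |
| 26 | 0.389 | 3.12 | 0.31 | 0.62 | 0.93 |

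The range is therefore about 0.3–3.2 points, and 0.6–1.9 at μ = 20.

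**Fall with a second, ungated baseline.** Selection acts on the screening score only. The expected fall from the second score to the preoperative score is (r_SB − r_SP) × SD × λ, where r_SB is the screening–baseline correlation and r_SP the screening–preoperative correlation.

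- Constant correlation: r_SB = r_SP, so the fall is 0. Simulation agrees (0.0 at r = 0.7 and 0.8).
- Decaying correlation (0.8 screening–baseline, 0.65 baseline–preoperative, 0.6 screening–preoperative), μ = 20: the same-score fall is (1 − 0.6) × 6.38 = 2.55 and the second-baseline fall is (0.8 − 0.6) × 6.38 = 1.28, so half remains. At μ = 24 (SD × λ = 4.07) the figures are 1.63 and 0.81.

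**If the cut-off is applied again to the second score.** In simulation at μ = 20 the fall is 1.30 under constant r = 0.7 (against 1.94 simulated for the single score) and 2.20 under the decaying pattern (against 2.55). Most of the artefact returns.

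**SD of change (μ = 20, constant r).** Same score: variance = SD²(1 − r²) + (1 − r)² × Var(qualifying score), with Var(qualifying score) = 64 × (1 − 0.798²) = 23.3. At r = 0.7 this is 32.64 + 2.09 = 34.7, SD 5.89. With a second baseline it is 2 × 64 × 0.3 = 38.4, SD 6.20. At r = 0.8 the SDs are 4.90 and 5.06.

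**Response rate.** Taking response as a 50% fall (an assumption; the article refers only to standard thresholds), simulation at μ = 20 and r = 0.7 with no treatment effect gives 2.6% with the same score and 1.2% with a second baseline, a difference of about 1 percentage point.

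**Against sampling error.** With n = 20 and the same-score SDs of change (3.52, 4.90 and 5.89 at r = 0.9, 0.8 and 0.7), the 95% half-width is 2.093 × SD/√20 = 1.6, 2.3 and 2.8 points. The bias at μ = 20 (0.6, 1.3, 1.9) is smaller each time.

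**The case against.** The strongest reply is that the bias is disclosed and the claims are limited to match. The Discussion names regression to the mean, and the article says repeatedly that the clinical analyses are exploratory and not meant to establish efficacy. None of the criteria under Feasibility criteria uses MADRS-S change. This stands and limits the weight of the point. It does not answer it: the disclosure presents as inherent something that is partly a measurement choice.

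Three stronger readings are tempting, and the documents do not support them.

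- A reader might infer that the next trial will be underpowered. The Discussion envisages a randomised sham-controlled or comparative trial, in which regression to the mean is expected in both arms and largely cancels in the contrast. Harm follows only if the raw single-arm change is taken directly as the between-arm effect. The article mentions effect size estimation but does not say it will be used that way, and placebo response would make that use unsound even with a second baseline. If the successor keeps the same entry rule and baseline, the SD observed under that rule is also the relevant one.
- A reader might infer that a separate baseline removes the artefact completely. That holds only under constant correlation. Decay is plausible, because onboarding may follow screening closely while the preoperative score comes at week 8–10 or later.
- A reader might take the size as established. It rests wholly on assumed inputs. The 3.2-point end needs a screened mean six points below the cut-off together with the lowest reliability; if most diagnosed candidates score well above 20, the fall is only a few tenths of a point.

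Finally, this is a condensed article. The supplementary schedule and the participant flow figure are not shown, and either could contain a separate screening score.

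**Conclusion.** The point holds as a minor design improvement. On the article's text, the qualifying score and the week-0 baseline are the same measurement, so the mean change contains a downward component caused by selection, which baseline adjustment does not remove. The direction is certain on that reading. The size is not: about 0.3–3.2 points over the assumed range (mean 14–26, SD 8, reliability 0.7–0.9) and 0.6–1.9 at mean 20, which is below the sampling error at n = 20. Effects on the SD of change and the response rate are small. The primary feasibility and acceptability outcomes are untouched. Natural fluctuation and placebo effects would remain whatever is done about the baseline.

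**What to change.** Use one MADRS-S at screening for the criterion of 20 or more. Collect a second MADRS-S at onboarding, before the first session and as long after screening as the workflow allows. Do not re-apply the cut-off to it. Use only this second score as week 0 in all change, response and mixed-model analyses. In the Discussion, separate the selection component from the regression to the mean that remains.

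The cost is one extra self-report form per participant, which can be completed remotely under the existing arrangements. Some week-0 scores will fall below 20 (in simulation at mean 20 and SD 8, about 14%, 20% and 25% at reliability 0.9, 0.8 and 0.7), and the reported mean change will be slightly smaller. If the full protocol already separates the two scores, one clarifying sentence in the article is enough.
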